#### Secondary outcomes

For all vaccinated participants, we will collect information on 2-dose completion according to the 0-month and 6-month schedule for HIV-negative MSM and the 0-month, 1-month and 6-month schedule for participants with HIV. Vaccination completion will be reported as proportions with 95% CIs from a binomial distribution. Using logistic regression analysis, we will assess determinants of completing the vaccination schedule among those who received a first HPV vaccination.

We will assess the proportions of HPV-16 and HPV-18 anal positive men and assess the proportions that are both HPV DNA-negative and seronegative for HPV-16 and for HPV-18 at baseline, both in group 1 and in group 2. This proportion gives an indication of the proportion of men at immediate risk of vaccine-type infection and hence to achieve direct benefit from vaccination. Using logistic regression analysis, we will assess determinants of anal HPV-16/18 infection and also of combined anal DNA-positivity and seropositivity.

In group 1, we will assess the proportions who have seroconverted, separately for each HPV type included in the vaccine. We will assess the geometric mean concentration (GMC) of type-specific antibodies and assess the impact of various baseline variables (like age, number of lifetime sexual partners, report of anal sex, Ab status at baseline, HPV DNA status at baseline) on the GMC, using multivariable linear regression analysis of (if needed log-transformed) HPV-16 and HPV-18 antibody concentrations separately.

For group 1 participants, we will assess how HPV-16/18 positivity 24 months after start of vaccination is affected by their HPV DNA and HPV antibody status just prior to vaccination. This will be done by calculating type-specific positivity rates, stratified by baseline DNA and antibody status and by estimating the effect of both homologous and heterologous DNA or antibody positivity at baseline on type-specific positivity rates at 24 months. We previously estimated a 24-month clearance probability of 65% for prevalent HPV-16 infections in HIV-negative MSM in Amsterdam, with a median age of 38.^28 41^ These analyses could shed light on the effectiveness of prophylactic vaccination in relation to prevalent infection or prior exposure to HPV at the moment of vaccination.

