### Study population

In the Netherlands, the bivalent HPV vaccine is routinely offered to preadolescent girls since 2009 and vaccination was extended to boys in 2022. In 2023, a catch-up campaign was launched to offer the bivalent vaccine to all unvaccinated individuals up to the age of 26 years. The vaccination programme uses a 2-dose schedule in accordance with the Dutch national vaccination programme,^31^ that is, vaccine is given at month 0 and at month 6. People with HIV or other causes of immunosuppression are given an extra dose at month 1.

The HPV4M study was initiated during the national catch-up campaign, but was conducted independently. During the study period, HPV vaccination was available at the same clinic through that national catch-up campaign. The age restriction in the HPV4M study is based on the minimum and maximum age within the national catch-up programme.

Participants are recruited at the SHC of Amsterdam in two phases. During the first recruitment phase, MSM born between 1 January 1996 and 31 December 2003 (aged 19–26 years at the start of the catch-up campaign) attending the SHC and accepting HPV vaccination were invited to participate (group 1). MSM were defined as individuals who were assigned male sex at birth, had not undergone genital gender-affirming surgery, regardless of their current gender identity, and who reported having had sex with partners with a penis in the past 6 months. See table 1 for remaining eligibility criteria. Of note, vaccination leads to seroconversion and very high antibody concentrations in the large majority of people with HIV also.^32^,^36^ Therefore, we did not exclude MSM with HIV from participation. For participants with HIV, CD4 cell counts and HIV viral load data are collected. The expected number of MSM with HIV in this age group is low (<5% of eligible men), so stratified analyses by HIV status will not be feasible. In the analysis, we will conduct a sensitivity analysis excluding people with immunocompromising conditions or the use of immunosuppressive medications or HIV infection.

**Table 1 T1:** Overview of eligibility criteria for group one and group 2, HPV4M study, Amsterdam, the Netherlands, 2023–2026

Inclusion criteria	
Group 1	Group 2

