At month 6, participants receive their last vaccine dose. Participants who missed a scheduled dose are contacted by phone and mail to reschedule the appointment as soon as possible. Samples for testing are collected neither at month 1 (for participants with HIV) nor at month 6. At month 15, participants complete a short online questionnaire about sexual behaviour and AEs. During the 24 month visit, participants are asked to complete the same online questionnaire and provide the same anal, penile, oral and blood samples as during the initial appointment. Participants who have missed their 6-month (or 1-month dose in case of immunocompromised individuals and people with HIV) vaccine dose are offered vaccination during the 24-month study visit. Study participation is completed after this visit. When all study visits are completed, participants interested in their serological response and anal HPV status will receive their results by mail, along with careful interpretation.

### Group 2

Group 2 will be recruited in the same calendar period when group 1 participants return for their 24-month visit. Men from group 2 will provide the same (anal, penile, oral gargle, venous blood) samples for HPV testing and complete the same questionnaire as group 1. Participation in group 2 consists of one single study visit.

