We will provide both intention-to-treat (ITT) and PP estimates of VE. In the ITT analysis, all individuals who are recruited into group 1 and return for the month 24 visit will be included. In the PP analysis, we will only consider group 1 participants who received all vaccine doses in the recommended intervals. Recommended intervals are 5–12 months after the first dose for the 6-month dose, and 3–6 weeks after dose 1 for the 1-month dose in immunocompromised individuals.^45 46^ In a sensitivity analysis, we will also calculate VE among the subgroup of PP participants with confirmed antibody response at month 24. Our primary analyses will be based on complete data for HPV-16/18 infection outcomes, using model-based imputation to handle any missing data for possible confounders (ie, covariates). In a sensitivity analysis, we will use model-based imputation for missing HPV-16/18 infection outcomes, to assess the effect of potential selective drop-out in Group 1 participants from baseline to month 24.

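### Vaccination completion is defined by HIV status alone, although the schedule and missed-dose rule also assign the month-1 dose to men with other immunosuppression

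*Protocol article*

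**What the plan says.** All references are to the protocol article.

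- **Study population** describes a two-dose programme at months 0 and 6 and adds: "People with HIV or other causes of immunosuppression are given an extra dose at month 1".
- **Procedures and interventions, Group 1** treats the month-1 dose as one that either group can miss. Its catch-up rule for a missed month-6 dose continues: "or 1-month dose in case of immunocompromised individuals and people with HIV) vaccine dose are offered vaccination during the 24-month study visit". An earlier sentence in the same section, on when samples are not taken, links the month-1 visit to participants with HIV only.
- **Statistical analyses, Primary outcomes** defines the per-protocol (PP) set: "we will only consider group 1 participants who received all vaccine doses in the recommended intervals". The intervals are "5–12 months after the first dose for the 6-month dose, and 3–6 weeks after dose 1 for the 1-month dose in immunocompromised individuals". HIV is not named separately there.
- **Statistical analyses, Secondary outcomes** defines the completion endpoint as "2-dose completion according to the 0-month and 6-month schedule for HIV-negative MSM and the 0-month, 1-month and 6-month schedule for participants with HIV". It continues: "Vaccination completion will be reported as proportions with 95% CIs from a binomial distribution". Determinants of completion are to be modelled by logistic regression.

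The Objectives list completion of the schedule among the secondary aims.

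**The concern.** The completion rule splits men by HIV status. The schedule splits them by HIV or any other cause of immunosuppression. The two splits disagree for one group: men who are HIV-negative but immunosuppressed for another reason. The completion rule asks two doses of them, whereas the schedule and the missed-dose rule assign three.

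Such men can be enrolled. Table 1 does not exclude them, and the Study population section plans a sensitivity analysis that removes immunocompromising conditions and immunosuppressive medication as items separate from HIV.

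At stake are the completion proportion and the outcome variable of the determinants model. Both would record some men as complete who had missed an assigned dose. The error runs one way only, towards higher completion. The endpoint is also labelled as two-dose completion although one of its branches has three doses.

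**Working it through.** **Step 1. Compare the sections on one man.** Take an HIV-negative immunosuppressed man who received doses at months 0 and 6, both on time, but none at month 1.

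| Section | Rule for the month-1 dose | His status |
|---|---|---|
| Study population | HIV or other immunosuppression | An assigned dose was not received |
| Group 1, missed-dose rule | Immunocompromised or HIV | Missed a dose |
| Group 1, sampling sentence | Mentions HIV only | No month-1 visit implied |
| Primary outcomes, PP set | Window for immunocompromised individuals | Outside PP |
| Secondary outcomes, completion | HIV only | Complete |

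**Step 2. Identify who is affected.** Among HIV-negative immunosuppressed men, one who received all three doses is complete under either rule. One who did not receive the month-6 dose is incomplete under either rule. Only those with months 0 and 6 but not month 1 change status.

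**Step 3. Size.** The article gives no completion figure to reproduce, so this is a bound.

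Inputs:
- Group 1 size is 431 (Project status).
- The share q of HIV-negative immunosuppressed men is not stated. Assumed 1–2%.
- The fraction m of those men who lack only the month-1 dose is not stated. Taken as 100% for the upper bound and 30% as a milder case.

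Formulas: men reclassified = 431 × q × m; shift in completion = 100 × q × m percentage points.

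- q = 1%, m = 100%: 431 × 0.01 = 4.3 men, 1.0 point.
- q = 2%, m = 100%: 431 × 0.02 = 8.6 men, 2.0 points.
- q = 1%, m = 30%: 431 × 0.01 × 0.30 = 1.3 men, 0.3 points.
- q = 2%, m = 30%: 431 × 0.02 × 0.30 = 2.6 men, 0.6 points.

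As a stress test, q = 5% with m = 30% gives 431 × 0.05 × 0.30 = 6.5 men, 1.5 points. With q = 5% and m = 100% it gives 21.6 men, 5.0 points, but nothing in the article suggests values that extreme.

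**Step 4. Compare with sampling error.** At an assumed 80% completion, the 95% CI half-width is 1.96 × √(0.80 × 0.20 / 431) = 0.038, or 3.8 points. The shift under the 1–2% assumption is smaller than this even at its upper bound.

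**Step 5. Check what does not move.** The sample size rests on assumed HPV-16 and HPV-18 prevalences, not on completion. The intention-to-treat estimate includes every group 1 man who returns at month 24. The PP set is defined by its own sentence and does not use the completion endpoint.

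**The case against.** The strongest reply is that the completion sentence is shorthand. The article's wording for the three-dose group is loose throughout: HIV only in one sentence of the Group 1 section, immunocompromised men and men with HIV in another, and immunocompromised individuals alone in the PP definition. On that view nobody meant to count immunosuppressed HIV-negative men as complete after two doses. That may well be the intention. But the completion sentence is a stated endpoint rule, and an analyst who applies it literally gets an answer that conflicts with the schedule. This is not detail left to an analysis plan.

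A reader might also infer a second conflict, over dose timing. The PP set accepts the month-6 dose only in a window ("Recommended intervals are 5–12 months after the first dose for the 6-month dose, and 3–6 weeks after dose 1 for the 1-month dose"), the completion rule states no window, and men who missed a dose "vaccine dose are offered vaccination during the 24-month study visit". The documents do not support calling this a contradiction:

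- The windows define an analysis set for vaccine effectiveness. Completion is an uptake outcome among all vaccinated men and may legitimately differ from that set.
- Men offered a dose at month 24 are already described as having missed theirs, so the natural reading is that this dose is not completion on schedule.
- An exact window for a secondary endpoint can be left to an analysis plan that is not shown.
- The article gives no share of late doses, so no size can be put on the issue.

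**Conclusion.** The point holds as an inconsistency about who is on the three-dose schedule. The completion endpoint uses HIV status alone, while the schedule and the missed-dose rule add other immunosuppression and the PP definition refers to immunocompromised individuals. One identifiable type of participant is therefore complete in one section, short of a dose in two others, and outside PP in a fourth.

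The effect is small. It is at most 4–9 men and about 2 points of completion if 1–2% of group 1 are HIV-negative and immunosuppressed, and probably well below 1 point, because not all of them will lack only the month-1 dose. Both the share and the fraction are assumptions. The consequence is confined to a secondary endpoint and its determinants model.

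It does not follow that completion must match the PP windows, or that the reported figure could be wrong by a wide margin. Nor does this point say which schedule is clinically right.

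**What to change.** 1. Reconcile Study population, the two Group 1 sentences, the PP definition and the completion definition to one description of who is on the two-dose schedule and who is on the three-dose schedule. The sponsor decides which description applies.
2. In Secondary outcomes, define completion as receipt of every dose on the participant's assigned schedule. Use that definition for both the proportion and the logistic regression of determinants.
3. Drop the two-dose label where the branch has three doses.

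The cost is a few words, with no extra visits or samples. The PP analysis already needs dose timing. The planned sensitivity analysis implies that immune status is known, although the Clinical data list names HIV status and not other immunosuppression, so the sponsor should confirm that it is recorded. Results are expected in late 2026. The change should be made before the completion analysis is run.

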### Patient and public involvement

Patient and/or public were involved in the design of this research. Representatives were selected from the target community to contribute ideas and provide input on the design and recruitment of participants, ensuring that the perspectives and interests of the target population were considered.

### Ethics and dissemination

This study has been reviewed and approved by the Medical Ethics Committee of the Amsterdam University Medical Center and registered accordingly in the European Clinical Trials Information System (2022-502224-49-00).

Data collected in this study are pseudonymised at the point of entry (inclusion visit) and stored on a secured folder with access restricted to the principal investigator and research personnel. After data collection, data from the questionnaires, SHC of Amsterdam and laboratory are merged based on unique study numbers. Data are checked for completeness and accuracy, and all analyses are version-controlled. At the end of the study, anonymised datasets and analysis code will be archived for future reference and may be made available to other researchers on reasonable request and ethics approval. The data will be stored for 25 years and the laboratory samples for 10 years.

The study protocol is made public through this protocol paper. Findings from this study will be published in peer-reviewed journals and presented at both national and international conferences. The study design was presented as a poster at the International Papillomavirus Conference in Edinburgh in November 2024. In terms of knowledge translation, the empirical evidence obtained with this study could provide insights for policymakers in the Netherlands and elsewhere. Therefore, results will be presented to stakeholders in immunisation policy and be shared through media aimed at a broad audience.

## Discussion

Targeted vaccination programmes for MSM could provide substantial health benefits, as they face high risk of HPV infections and related diseases, particularly anal cancer.^2 3 9 10^ The efficacy of vaccinating MSM up to 26 years of age with limited prior exposure to HPV is high,^21^ but estimates of real-world effectiveness vary, likely due to variations in study design, in particular regarding prior HPV exposure among study participants.^22^,^2647^ Previous studies lacked prevaccination HPV DNA data and antibodies data and often had to rely on self-reported vaccination status or included individuals who were very recently vaccinated; all these factors impact VE estimates. Furthermore, VE estimation in HPV-exposed populations is highly dependent on the proportion of prevalent infections, the clearance rate, natural immunity and ongoing HPV exposure. The HPV4M study addresses these knowledge gaps by evaluating the effectiveness of the bivalent HPV vaccine at population level among young MSM visiting the SHC of Amsterdam. Our findings can answer the question of whether targeted HPV vaccination programmes for MSM up to age 26 years are effective, in order to improve control of HPV-related cancer in MSM.

This study has several strengths. First, the cross-sectional design with a longitudinal component allows efficient VE assessment. The longitudinal component for vaccinated participants provides valuable prevaccination data, minimises bias from self-reported vaccination status and enables us to define the exact time between vaccination and HPV sampling. Furthermore, it is crucial to allow an appropriate clearance period to prevent underestimation of VE due to prevalent infections at the time of immunisation. As such, the 24-month follow-up in this study is based on the 24-month clearance probability of 65% in a previous Dutch study among older HIV-negative MSM (median age: 38 years, IQR 34–42).^38^ More recent studies among younger HIV-negative MSM have estimated 24-month clearance probabilities between 70% and 80%.^9 10^ Our assumption on clearance may therefore be conservative, but prevents us from underestimating the VE. Higher clearance than anticipated will only improve the statistical power of our study. Second, our extensive data collection allows us to correct for factors impacting VE and to identify potential confounders. A randomised controlled trial would have been the best approach to address the research question. However, randomisation was deemed unethical, as the study was integrated into an existing national HPV vaccination catch-up campaign and withholding vaccination would have been unfair to participants willing to get vaccinated. By recruiting all participants at the same SHC using the same approach and protocol, we increase comparability between the vaccinated and unvaccinated groups in the absence of randomisation. We anticipated that recruiting an unvaccinated control group during the campaign could introduce confounding, as those who choose to get vaccinated may differ systematically from those who do not, for example, in terms of health literacy and awareness of HPV-related risks. To address this, the unvaccinated group will be recruited at a later stage (when the HPV catch-up campaign is concluded) and will consist of men who missed the opportunity for HPV vaccination rather than those who explicitly declined it. Attendees were eligible for participation in group 2 of the study if they would be willing to get vaccinated if offered the vaccine at enrolment. Furthermore, the analysis will adjust for variables on which the two groups differ. Nevertheless, residual confounding may occur.

When assessing the sample size, we assumed that individuals with vaccine-type antibodies due to prior infections are not susceptible to new vaccine type infections. Some studies have suggested that naturally acquired antibodies after HPV infection reduce the risk of new infections among women.^48^ However, studies also found that the evidence of natural immunity among men was inconclusive^49^ or suggested lack of protection at naturally occurring antibody levels.^50^ It remains uncertain how long natural immunity lasts, if present at all in men, and what the impact of natural immunity is on vaccine-acquired immunity.^51^ We acknowledge that our assumption may be a simplification of the natural immunity. However, we expect that less immunity is likely to improve the statistical power of our study.

Two key challenges of this study are the potential LTFU among the vaccinated MSM (group 1) and the recruitment of a comparable control group. Regarding the latter, we will use age-matching on group level and recruitment in the same setting and time period to ensure a comparable age distribution and recent population exposure between the vaccinated and unvaccinated groups. Furthermore, we will test for comparability on variables like number of sexual partners, STI history, years of sexual activity, etc, and correct for possible confounders in multivariable analyses. The LTFU of group 1 will be minimised by ensuring personal engagement and attention with the participant, combining the follow-up visit with a regular STI visit and sending regular reminders if needed. Furthermore, our sample size of 430 for group 1 accounts for 30% LTFU, which is higher than observed in a similar study at the SHC of Amsterdam.^38^

The HPV4M study will evaluate whether vaccination programmes targeting MSM aged 19–26 years can effectively prevent newly acquired anal HPV-16/18 infections and hence HPV-related anal cancer. The results of our study can be used to project the population-level impact of HPV vaccination programmes, perform cost-effectiveness analyses of scaled-up HPV vaccination efforts and to inform policymakers in a timely manner regarding the desirability of campaigns targeting high-risk groups with similar HPV exposure (not necessarily restricted to MSM) in parallel with the National Immunisation Programme. If the project demonstrates that HPV vaccination is effective against new anal HPV infections in sexually active MSM up to 27 years of age, routine vaccination could be easily implemented by adding it to the existing targeted hepatitis B vaccination programme in SHC, which has a similar vaccination schedule.

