Although most effective when given prior to HPV exposure, HPV vaccination can still be effective when administered at later ages. The per protocol analysis of a vaccine efficacy trial among young MSM with no prior HPV exposure reported 94% efficacy against anal HPV-16 DNA detection at any time and 100% for HPV-18.^21^ Effectiveness among young MSM (ages 16–30 years) with prior HPV exposure is much lower, ranging from 45% to 70% for HPV-16^21 22^ and from 45% to 52% for HPV-18.^23 24^ One study even found a non-significant negative effectiveness against HPV-16 among MSM vaccinated between 18 years and 26 years.^24^ Several studies focused on vaccine effectiveness (VE) for all quadrivalent vaccine-targeted types combined, rather than separately assessing VE for HPV-16 and for HPV-18. Reported effectiveness ranged from 20% to 76% for grouped HPV-6/11/16/18,^2122 24^,^26^ with one study demonstrating no significant effectiveness.^23^ These heterogeneous results may be attributed to differences in study design, such as limiting inclusion criteria to participants with few sexual partners,^21^ excluding HPV-positive individuals at baseline,^21^ relying on self-reported HPV vaccination status^22^,^26^ or including people who had been vaccinated very recently among the vaccinated population.^22 26^ These aspects limit insights into the real-world VE as they can lead to overestimations or underestimations of the effectiveness in populations with prior exposure to HPV. Most studies on VE among MSM concerned the quadrivalent vaccine, few concerned the non-avalent vaccine^24^ and none the bivalent vaccine. A Dutch observational study assessed the impact of bivalent HPV vaccination at 12–16 years of age on anal HPV infections in women aged 18–26 years old, showing a 90% (95% CI: 63% to 97%) reduction in the risk of anal vaccine type HPV infections among vaccinated women compared with unvaccinated controls.^27^

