Being male and reporting sex with other men in the preceding 6 months Born between 1 January 1996 and 31 December 2003 (age 19–27 years during inclusion) Attending the SHC in Amsterdam Accepting prophylactic HPV vaccination (as routinely offered within the Dutch catch-up programme) Willing and able to return for a subsequent visit for vaccination Planning to stay in or around Amsterdam over the next 2 years Willing and able to complete an online questionnaire at month 15 Willing and able to return for a month 24 final study visit Providing informed consent	Being male and reporting sex with other men in the preceding 6 months Born between 1 January 1996 and 31 December 2003 (age 21–29 years during inclusion) Attending the SHC in Amsterdam Hypothetically accepting prophylactic HPV vaccination Providing informed consent

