**Exclusion criteria**	
Both group 1 and group 2	
Having been vaccinated with one or more doses of any HPV vaccine Not able to read/understand Dutch or English Previous enrolment in the study History of anal cancer or anal intraepithelial neoplasia (AIN) Unlikely to adhere to the study protocol in the opinion of the study physician Allergy to one or more components of the vaccine*	

* We asked patients whether they had ever experienced an allergic reaction to a vaccine or to specific components of any medication.

HPV, human papillomavirus; HPV4M, HPV vaccine effectiveness study among MSM; MSM, men who have sex with men; SHC, Sexual Health Center.

Group 1 will be followed up until 24 months after their first vaccination. In the calendar period that group 1 men return for their 24-month visits, an unvaccinated age-matched control population will be enrolled (group 2) (see figure 1 for schematic representation). Group 2 participants are recruited from the same birth cohorts as group 1 participants, enabling direct comparison of the prevalence of anal HPV-16 and HPV-18 infections between the vaccinated (group 1) and the unvaccinated (group 2) participants. During the recruitment period for group 1, HPV vaccination was available free of charge through the national catch-up campaign for all individuals up to the age of 26 years. Group 2 is recruited after the campaign was concluded, and free vaccination was no longer available. Group 2 participants were asked about their reasons for not having received the HPV vaccine. Participants were eligible for participation in group 2 of the study if they would be willing to get vaccinated if offered the vaccine at enrolment.

Ideally, the study population is representative of all MSM aged 19–26 years attending the SHC at the Public Health Service of Amsterdam, in terms of sexual orientation (eg, sex with only men, sex with both women and men), ethnicity, education, socioeconomic status, number of sexual partners, HPV infection status, presence of coinfections (eg, HIV) and past STIs. However, enrolled participants may differ from this population, as participation depends on willingness and ability to participate in this study. To address this, we will collect information on the above-mentioned variables for both study groups and compare their distribution with that of the reference population from the SHC of Amsterdam.

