### Procedures and interventions

When a potential participant (either group 1 or 2) meets with a research nurse, the study is explained and eligibility criteria are assessed. If he decides to participate, both the participant and research nurse sign two copies of an informed consent form, which includes a Patient Information Form; one copy is kept for our records and the other is given to the participant. Since Group 1 is followed up for 24 months, and participation in Group 2 only consists of a single visit, both procedures are explained separately below.

### Group 1

During the first visit (month 0), participants are asked to complete a short online questionnaire on an SHC-provided tablet (further explained in the Questionnaires section). Next, the nurse explains the sampling procedures, and the participant provides anal, penile and oral rinse self-samples. For the anal swab, participants insert the swab 3 cm into the anal canal and turn it around for 5–10 s. For the penile swab, participants rub the swab firmly over the skin of the penile shaft, including the outside of the foreskin, for 20 s (ie, 5 s per side). For the oral rinse samples, participants rinse their mouth with a saline solution for 30 s, collecting cells and viral particles from the oral cavity and oropharynx. Finally, the nurse collects 5 mL venous blood. If needed, the visit is combined with a regular STI visit (eg, PrEP consultation, STI tests or treatment). After sample collection, the first dose of the bivalent HPV vaccine, Cervarix, is administered. The next appointment (at month 6 and, if necessary, at month 1) is scheduled during this appointment.

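### The Discussion describes group 2 as men who missed rather than declined vaccination, but the eligibility criteria do not guarantee this

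*Protocol article*

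**What the plan says.** The Discussion explains why controls were not recruited during the campaign: men who choose vaccination may differ from those who do not, for example in health literacy and awareness of HPV-related risks. As the remedy, group 2 is recruited later and "will consist of men who missed the opportunity for HPV vaccination rather than those who explicitly declined it". The next sentence there gives willingness to be vaccinated at enrolment as the eligibility condition.

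In Table 1 (Study population), the group 2 criterion on willingness is "Hypothetically accepting prophylactic HPV vaccination". An exclusion that applies to both groups is "Having been vaccinated with one or more doses of any HPV vaccine". No criterion refers to an earlier refusal.

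On the setting, Study population says "During the study period, HPV vaccination was available at the same clinic through that national catch-up campaign", and that vaccination under the campaign was free. It adds: "Group 2 is recruited after the campaign was concluded, and free vaccination was no longer available".

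On the reason for remaining unvaccinated, the same section says "Group 2 participants were asked about their reasons for not having received the HPV vaccine". The Questionnaires section repeats that this item is collected. The article gives it no role in eligibility or in the analyses it describes.

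**The concern.** The Discussion states as fact who is in the control group and uses that fact to argue that a named source of confounding has been dealt with. Willingness now and refusal then are different things. Asking about willingness at enrolment removes men who still refuse. It does not remove men who refused in 2023–24 and have since changed their minds.

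If such men are in group 2, part of the difference between acceptors and decliners that late recruitment was meant to avoid returns to the comparison. The variables listed under Clinical data cover demographics, general health and sexual behaviour. Education, work status and income may act as proxies, but neither health literacy nor awareness of HPV risk is listed, so the adjusted model may not reach the two confounders that the Discussion names. The full questionnaires are in a supplement that is not at hand, so this last point rests on the article's list alone.

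What is at stake is bias in VE, of unknown direction, and a description of the control group that readers will take at face value.

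**Working it through.** **1. The statement against the rules**

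| Source | What it fixes for group 2 |
|---|---|
| Discussion | Missed the opportunity; did not explicitly decline |
| Table 1, inclusion | Would accept vaccination if offered at enrolment |
| Table 1, exclusion | No dose of any HPV vaccine |
| Study population | Free vaccination had been available at this clinic during the campaign |

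Take a man from the eligible birth cohorts who attended this clinic during the campaign, refused the vaccine, has had no dose since, and would now accept. If he meets the remaining criteria, he is eligible. The Discussion says that such men are not in group 2, and no rule keeps them out.

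**2. The plan's own figures**

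Inputs (Sample size calculation): prevalence 13.9% (HPV-16) and 11.3% (HPV-18) in group 2; month-24 prevalence 6.2% and 4.6% in group 1; two-sided alpha 0.05 (sidedness is not stated, but two-sided reproduces the figures); power 80%; 300 analysed per group.

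- The continuity-corrected two-proportion formula gives 264 and 284 per group, as stated.
- HPV-16: OR = (0.062/0.938)/(0.139/0.861) = 0.0661/0.1614 = 0.41, so VE = 59%.
- HPV-18: OR = (0.046/0.954)/(0.113/0.887) = 0.0482/0.1274 = 0.38, so VE = 62%.

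These figures are not in dispute.

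**3. Illustration of the possible shift**

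The documents give neither the share f of earlier decliners in group 2 nor their odds ratio r of infection relative to the other group 2 men. Both are assumed here. The other men are given the planned prevalence p, and no adjustment is applied.

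- Odds among decliners = r × p/(1 − p); prevalence among decliners = odds/(1 + odds).
- Group 2 prevalence = (1 − f) × p + f × (prevalence among decliners).
- Apparent VE = 1 − (odds in group 1)/(odds in group 2).

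Example for HPV-16 with f = 25% and r = 1.5: decliner odds = 1.5 × 0.1614 = 0.2422, prevalence 0.195. Group 2 prevalence = 0.75 × 0.139 + 0.25 × 0.195 = 0.153, odds 0.1806. OR = 0.0661/0.1806 = 0.366, so VE = 63.4%.

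| f | HPV-16 VE, r = 0.67 | HPV-16 VE, r = 1.5 | HPV-18 VE, r = 0.67 | HPV-18 VE, r = 1.5 |
|---|---|---|---|---|
| 0 (plan) | 59.1% | 59.1% | 62.2% | 62.2% |
| 10% | 57.6% | 60.9% | 60.8% | 63.9% |
| 25% | 55.2% | 63.4% | 58.6% | 66.2% |
| 50% | 50.7% | 67.0% | 54.5% | 69.6% |

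**4. Scale against sampling error**

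At 300 per group, the expected HPV-16 counts are 18.6 positive and 281.4 negative in group 1, and 41.7 and 258.3 in group 2.

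SE(log OR) = √(1/18.6 + 1/281.4 + 1/41.7 + 1/258.3) = 0.292.

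With log OR = −0.893, the 95% interval is −0.893 ± 1.96 × 0.292, which gives a VE of about 27% to 77%.

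**5. Precision of a sensitivity analysis without decliners**

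If 25% of group 2 were excluded, 225 would remain, with expected HPV-16 counts of 31.3 positive and 193.7 negative. SE = √(1/18.6 + 1/281.4 + 1/31.3 + 1/193.7) = 0.307, against 0.292 with all 300. At 50% excluded (150 remaining) it would be 0.336.

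**The case against.** The case on the other side has several parts.

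*The design already does much for comparability.* Controls come from the same clinic, birth cohorts and calendar period. Persistent refusers are screened out, adjustment is planned, and confounding is conceded both in the strengths and limitations and in the Discussion. This stands. A reader might infer from the gap that the groups are not comparable, but the documents do not show that. They show only that one stated property of group 2 is not secured. A general concession of residual confounding does not, however, correct a specific statement about who was enrolled.

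*Use of the reason item may be set out in the analysis plan.* It may, and that plan is not at hand, so the article's silence on it is not the finding. The finding is that the Discussion sentence and the Table 1 criteria do not agree, and an analysis plan cannot change that.

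*Refusals are recorded.* The Recruitment section notes men who decline so that they are not approached again. That record concerns refusal of the study, not of the vaccine, and flyers and social media are further routes in.

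*Vaccination status.* A reader might also infer that unvaccinated status is not enforced in group 2, since the Introduction counts "relying on self-reported HPV vaccination status" among the possible explanations for differing results elsewhere. The documents do not support this. Any prior dose is an exclusion in both groups, and when a candidate meets the research nurse "the study is explained and eligibility criteria are assessed". The source used to check this may be in the full protocol. The Discussion's claim to reduce self-report bias is made for the vaccinated group only.

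*The shift is small beside the sampling error.* This is true for the smaller assumed shares. But bias, unlike sampling error, is not reflected in the confidence interval.

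**Conclusion.** The concern holds in a limited form. The missed-not-declined description of group 2 is asserted, and the eligibility criteria do not guarantee it, because an earlier decliner who would accept now is eligible. Since the Discussion relies on that description to answer a named confounder, the sentence should be corrected and its influence on VE checked.

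The size cannot be established from the documents. With assumed shares of 10% to 50% and assumed odds ratios of 0.67 or 1.5, the unadjusted HPV-16 VE of 59% would read anywhere from 51% to 67%, and the HPV-18 VE of 62% from 55% to 70%. If few controls had declined, or if decliners' HPV risk matched that of the other men, there would be almost no shift. The sample size is not affected.

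**What to change.** - Use the reason for non-vaccination already collected from group 2 to classify each man as having missed or declined an earlier offer, and report the number of each.
- Before analysis, specify a sensitivity VE estimate for HPV-16 and for HPV-18 that excludes recorded decliners. Keep the primary control set as it is.
- Reword the Discussion sentence: group 2 consists of unvaccinated men who were willing to be vaccinated at enrolment, some of whom may have declined an earlier offer.

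No new data are needed if the reason item separates refusal from a missed opportunity. The cost is some precision in the sensitivity analysis (SE of the HPV-16 log OR 0.307 instead of 0.292 if a quarter of controls were excluded) and reliance on a self-reported reason.

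Two stronger remedies are not advised. Removing decliners from the primary control set would change the comparison while recruitment is under way. Dropping controls whose antibody levels resemble those of group 1 could remove men with naturally acquired antibodies, and so select on a correlate of the outcome.
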